**Blended CBT (bCBT)**

In the bCBT group, patients receive 6-10 face-to-face sessions and 6-10 internet sessions, which will be delivered over a period of 12-20 weeks. Treatment starts and ends with a face-to-face session. The online sessions are delivered through a secured web-based online treatment platform (Minddistrict; www.minddistrict.com). Patients access this platform with a personalized login. The website offers information that repeats and extends the contents of the face-to-face sessions. In addition, patients use the website to complete homework exercises, such as monitoring their activities, feelings, thoughts and behavior. The first online session focuses on working with the online platform. The therapist monitors patients’ online progress and provides weekly feedback prior to the next face-to-face session. Face-to-face sessions will be audio-recorded and checked, following the same procedures as in the CBT-TAU condition. Online sessions are recorded in the online treatment platform database. On completion of treatment, patients can still access the online treatment platform to re-read information and look up homework exercises, such as the relapse prevention plan.

The same medication regimes will be administered for both conditions throughout the study. Pharmacotherapy falls under the responsibility of a psychiatrist and is provided independently of the current study.

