### The Beck Anxiety Inventory (BAI) (Beck et al., 1988)consists of twenty-one questions about how the subject has been feeling in the last week, expressed as common symptoms of anxiety (such as numbness and tingling, sweating not due to heat, and fear of the worst happening). It is designed for an age range of 17–80 years old. Each question has the same set of four possible answer choices, which are arranged in columns and are answered by marking the appropriate one with a cross. The BAI has a maximum score of 63. For this study, treatment response is defined as a symptom reduction of the baseline BAI symptom severity score of at least 30% and remission a score reduction of at least 30% reduction plus a total score <11.

**The EQ-5D-3L** (EuroQol, 1990; Lamers, 2005) will be administered at every assessment moment (T0-T3) to assess *general well-being*. The questionnaire consists of five questions that tap mobility, self-care, daily activities, pain and mood. Each item has three response categories, ranging from 0 (*no problems*) to 3 (*severe problems*). In addition to this, participants use a VAS scale to rate their health on a scale ranging from 0 (*worst possible health*) to 100 (*best possible health*). The answers on the five questions are combined in a number sequence that corresponds with the five answers, for example 03210. The total number of possible sequences is 3^5^=243. Each sequence stands for a certain health state. On these health states, a value (utility) has been placed (Lamers et al., 2006), which in turn is used to determine the quality-adjusted life years (QALYs). This is done by calculating the QALYs gained between the follow-up periods by weighing the length of time spent in a particular health condition by the utility score (Drummond, 2005).

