**Cost outcomes**
Cost estimates include 1) the costs of offering the treatments and 2) Patients’ out-of-pocket costs (non-medical), such as the costs of travelling to the health services and the patients’ time costs of travelling, waiting and receiving treatment, which are determined with the standard cost prices as listed in the pertinent Dutch guideline for economic evaluation (Tan et al., 2012). Furthermore, 3) Costs stemming from health care uptake, including costs of medication, and 4) Costs stemming from productivity losses due to absenteeism and lesser efficiency while at work (presenteeism) are assessed with *The Trimbos/iMTA questionnaire for Costs associated with Psychiatric Illness* (TiC-P; Hakkaart – van Roijen et al., 2002.

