### TiC-P is the most widely used health service receipt interview for economic evaluations in the Netherlands. The TiC-P consists of 46 questions, divided over two parts. Part 1 entails the health care uptake at relevant health care providers in the past 4 weeks, such as medication intake, and the number of contacts within the mental health care setting, with the GP and with other medical specialists. To determine the costs associated with these contacts, the care consumption is multiplied by the cost price described in the before mentioned guideline. Part 2 of the TiC-P entails loss of productivity in the past 4 weeks. This is measured by enquiring about the number of days absent from work and the number of days with reduced efficiency due to feeling ill. The costs of productivity losses will be based on the gender and age specific friction costs, as outlined in the Dutch guideline for costing (Hakkaart van Roijen L, 2010).

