**CEA/CUA**

Costs will be assessed at pre-, mid-, post-treatment and at one-year follow up. As the TIC-P cost date covers a period of three months, all costs will be extrapolated to a 12 months period assuming a stability of costs during the time frame. T-tests will test the change for each cost domain. As cost data will not be normally distributed, p-values will be estimated using a multilevel model (with repeated measurements to control for dependency between the measurements) after which a bootstrap analysis on the parameters is performed (10,000 replications, to generate a reliable cost estimate [23]. An incremental cost-effectiveness ratio (costs per case response or remission) and will be calculated (ICER =(mean costs blended eHealth treatment-mean costs TAU)/(mean bCBT -mean CBT-TAU). The mean costs, including all medical and non medical costs, of the patients in the blended eHealth condition will be subtracted from the mean costs of the patients in the TAU condition. This difference will be then be divided with the subtracted effects (case of response or remission on the BAI). This procedure will be bootstrapped 10,000 times, generating an estimation of the blended eHealth treatment groups’ incremental costs in relation to their incremental health benefit. Additionally an incremental cost-utility ratio (costs per QALY) will be calculated; this procedure is identical to the cost-effectiveness ratio with the exception that instead of a case of response or remission, an additional quality adjusted life year is calculated (QALY). Finally, to test the robustness of the results, we will conduct a sensitivity analyses, to investigate how sensitive the ICERs will be to changes of cost estimates (for example difference in costs per iCBT contact, type of psychologists and number of sessions). For decision-making purposes, the ICER acceptability curve will be plotted for various willingness-to-pay (WTP) ceilings, which helps making judgments about whether the blended intervention offers good value for money, relative to treatment as usual. One-way sensitivity analyses directed at uncertainty in the main cost drivers will be performed to gauge the robustness of our findings across a range of likely values of those parameters.

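### The primary economic analysis scales all costs to 12 months as if they were stable, which contradicts a 12-20-week therapy; recall period, session counting and cost horizon also need reconciling

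*Protocol*

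**What the plan says.** The rule stands in the Protocol's primary analyses, under CEA/CUA: "all costs will be extrapolated to a 12 months period assuming a stability of costs during the time frame". The same sentence gives its reason: "As the TIC-P cost date covers a period of three months". All medical and non-medical costs then enter the numerator of the ICER.

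Other parts of the Protocol bear on this rule:

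- **Therapy length.** The section on blended CBT describes face-to-face and internet sessions "which will be delivered over a period of 12-20 weeks". The usual-CBT section gives the same 12-20 weeks.
- **What the TiC-P covers.** Its description states a different recall: "Part 1 entails the health care uptake at relevant health care providers in the past 4 weeks". It includes "the number of contacts within the mental health care setting".
- **When it is taken.** Table 1 places it at baseline (T0), mid-treatment (T1, week 6-10), end of treatment (T2, week 12-20) and follow-up (T3, week 64-72).
- **Treatment costs.** The cost outcomes section lists them as an item of their own: "Cost estimates include 1) the costs of offering the treatments". Only health care uptake and productivity losses are assigned to the TiC-P.
- **QALYs.** The EQ-5D-3L is administered at T0-T3, and QALYs are obtained by "calculating the QALYs gained between the follow-up periods by weighing the length of time spent in a particular health condition".

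The planned sensitivity analyses vary cost estimates (cost per internet contact, type of psychologist, number of sessions, main cost drivers). None varies the extrapolation or the time horizon.

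**The concern.** A constant-cost assumption suits a stable chronic condition with steady service use. Here the four cost measurements fall before, during, at the end of, and about a year after a time-limited therapy, so mental-health contacts should rise and then fall. Those contacts are also where the arms differ most by design. Projecting a treatment-phase measurement over a year would enlarge both the therapy cost and the between-arm difference in it.

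Three further matters attach to the same sentence: two recall periods that cannot both be right, a possible double count of study sessions, and a cost period that does not match the span of the QALY measurements. Exploring health-economic outcomes is the trial's main goal (Objectives section), so this sentence shapes the primary result rather than a side analysis.

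**Working it through.** The plan reports no figure that results from the extrapolation, so there is none to reproduce on this point. The sample size does not rest on it: with the stated inputs, 2 × (1.96 + 0.84)² × 2,944,000 / (1,600 − 832)² = 78.26 per group, against 78 stated.

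**1. Annualising therapy contacts**

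Inputs: therapy of 12 or 20 weeks; T1 at week 6 or 10; T2 at week 12 or 20; recall of three months (13 weeks, scale factor 4) or 4 weeks (scale factor 52/4 = 13). Assumptions: one session a week, no therapy contacts in the T0 or T3 windows. Inflation = annualised sessions / sessions delivered.

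| What is scaled | Three-month recall (×4) | 4-week recall (×13) |
| --- | --- | --- |
| T1 only | 6 × 4 = 24 against 12, or 10 × 4 = 40 against 20: 2.0 | 4 × 13 = 52 against 12 or 20: 4.3 or 2.6 |
| T2 only | 12 × 4 = 48 against 12: 4.0; 13 × 4 = 52 against 20: 2.6 | 52 against 12 or 20: 4.3 or 2.6 |
| Mean of T0-T3 | (0 + 24 + 48 + 0)/4 = 18 against 12: 1.5; (0 + 40 + 52 + 0)/4 = 23 against 20: 1.15 | (0 + 52 + 52 + 0)/4 = 26 against 12 or 20: 2.2 or 1.3 |
| T3 only | 0: no inflation | 0: no inflation |

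The top of the range is 52/12 = 4.33. Under a 4-week recall with evenly spread sessions, the T1 and T2 factors are 52 divided by the weeks of therapy, whatever the session frequency: 20 sessions in 12 weeks become 86.7 a year, again 4.33-fold.

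**2. Recall period**

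Scaling by 13 or by 4 differs by 13/4 = 3.25. If the questionnaire covers 4 weeks but is scaled as three-month data, every yearly TiC-P cost is 3.25 times too low, in both arms and for all cost items.

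**3. Counting of study sessions**

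Treatment cost is one item. Health care uptake from the TiC-P is another and includes mental-health contacts. Both belong to the total. No sentence removes study sessions from the TiC-P contacts, so they can be counted twice.

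**4. Time horizon**

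Time-weighting utilities over T0-T3 gives a span of 12 + 52 = 64 to 20 + 52 = 72 weeks. Costs are set to 52 weeks.

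- Share of the QALY span covered by costs: 52/64 = 81.3%; 52/72 = 72.2%.
- If weekly differences in cost and utility are constant, cost per QALY is too small in absolute size by 1 − 0.813 = 19% to 1 − 0.722 = 28%.

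**5. Direction**

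Annualising T1 or T2 enlarges a saving from fewer face-to-face contacts. Setting 52 weeks of costs against 64-72 weeks of QALYs shrinks a continuing cost difference to 72-81% of its size. If blended CBT saves money, these two effects work against each other.

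**The case against.** The CEA/CUA section does not say which of the four measurements is scaled or how they are combined, and a combination rule may properly sit in the statistical analysis plan. If only T3 is scaled to stand for the follow-up year, and therapy is costed separately from session counts, no therapy is multiplied. The separate cost item, the contact counts and time records listed under Process data, and a sensitivity analysis on number of sessions all fit that reading.

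This stands, and it rules out several stronger readings. A reader might infer that:

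- every TiC-P measurement is blown up to a year, with a 2.6- to 4.3-fold inflation. That is the upper part of the range under an unstated rule, not an estimate of the bias;
- the error must favour blended CBT. The text does not settle this, since the horizon effect can run the other way. A bare count of face-to-face sessions also ignores therapist time spent on online feedback;
- sessions are counted twice. The text leaves this open but does not say so;
- the Protocol fixes a 64-72-week QALY horizon. This is inferred from the assessment schedule and the time-weighting; no horizon is stated for the CUA. It also does not touch the ICER per response or remission.

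The objection does not rescue the rule itself. The stability assumption is stated, not left open. Scaling only T3 omits non-therapy costs during the 12-20 treatment weeks and still does not match QALYs that start at T0. The two recall periods conflict under any reading.

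**Conclusion.** The point holds in this form. A stated primary-analysis rule assumes stable costs over 12 months, the design contradicts that assumption, and no planned sensitivity analysis tests it. The overstatement of therapy contacts ranges from none (T3 only), through about 1.2- to 1.5-fold (mean of T0-T3) and 2.0- to 4.0-fold (T1 or T2) under a three-month recall, to 4.3-fold under a 4-week recall. These figures assume weekly sessions and no therapy in the T0 and T3 windows. The net direction cannot be determined from the document.

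The recall conflict is a plain contradiction worth a factor of 3.25. Double counting is possible, not shown. The horizon mismatch is worth 19-28% of cost per QALY if QALYs run over T0-T3 and weekly differences are constant.

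**What to change.** - State one TiC-P recall period in both places, matching the questionnaire actually used, and scale by it.
- Cost study therapy once, from session records and platform usage logs, and exclude those sessions from the TiC-P mental-health contacts.
- Convert the remaining TiC-P costs to a rate at each of T0-T3 and integrate these rates over time.
- State a single horizon and use it for both costs and QALYs.
- Keep the 12-month stability extrapolation as a sensitivity analysis only.

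The cost is revised analysis wording and a little more programming. No new data are needed: the TiC-P and EQ-5D share the T0-T3 schedule, and contacts, time investment and platform use are already listed as process data. Two limits remain. Interpolating across the 52 weeks between T2 and T3 is itself an assumption and needs its own sensitivity analysis. A common cut-off at 64 weeks, if chosen, would drop up to 72 − 64 = 8 weeks for patients whose T3 falls at week 72.

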# STUDY DESIGN

The study is a cost-effectiveness study, designed as a parallel-group randomized controlled trial (N = 156), in which participants are randomly allocated to either bCBT (n=78) or CBT-TAU (n=78). Participants are recruited in Dutch specialized mental healthcare centers (GGZInGeest, GGZAltrecht or GGZ Oost Brabant), large scale mental health service organizations, respectively in the Amsterdam, Utrecht and Noord-Brabant region.

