# Measurements are taken at four fixed 6-10-week intervals (depending on the type of anxiety treatment); at baseline (T0), week 6-10, week 12-20 and at weeks 64-72 (52 weeks follow-up) (T1 – T3). The recruitment of participants aims to start April 2015 (first patient in; after Medical Ethics (METC) consent) and the inclusion ends at December 2016, and the follow up at December 2017. For detailed information on the sample size and power calculation, see the study protocol.

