## Sample size calculation

In economic evaluations we are calculating the power to estimate the joint distribution of costs and treatment effects. Subsequently, we need more information for estimating power compared to clinical trials, namely expected costs of treatments, expected covariance of treatment effects/costs, and the maximum willingness to pay for the treatment effect. To incorporate this information, the formula of Glick et al. (2011) can be used. A goal of sample size and power calculation for cost-effectiveness analysis is to identify the likelihood that an experiment will allow us to be confident that a therapy is acceptable or not when we adopt a particular willingness to pay.

For this study a sample size of 156 is based on a formula to estimate the power of a cost-effectiveness analyses. (Glick, 2011)

$$n=\frac{{2(z_{\alpha}+z_{\beta)}}^{2}\left( {sd}^{2}+\left( W^{2}{sd}^{2} \right)-\left( 2W\rho{sd}_{c}{sd}_{q} \right) \right)}{\left( WE-C \right)^{2}}$$

$$n=sample size/group$$

$$z_{\alpha}=z statistics for alpha$$

$$z_{\beta}=z statistics for Beta$$

$${sd}_{c}=Expected standard deviation costs$$

$${sd}_{e}=Expected standard deviation effects$$

$$W=Willingness to pay$$

$$C=Expected differences in costs$$

$$E=Expected differences in effects$$

$$\rho=correlation between differences in costs and effects$$

($z_{\alpha}=1,96$, $z_{\beta}=0,84$,${sd}_{c}=800$, ${sd}_{e}=0,02$, $W=80,000, C=832,E=0,02 \rho=0,1)$

Following the formula, we may expect that the point estimate for the cost-effectiveness ratio will be around 40,000 per quality- adjusted life year (QALY), using only a small increase in quality of life and lower costs for blended eHealth, we want to design an experiment that will provide an 80% chance (i.e., power) to be 95% confident that the therapy is good value when we are willing to pay at most 80,000 per QALY. In the Netherlands, a costs-effectiveness ratio between 20.000 and 80.000 Euro per QALY is assumed acceptable.

Glick, H.A. (2011). Sample size and power for cost-effectiveness analysis (part 1). Pharmacoeconomics, 29 (3), 189-198.

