## Randomisation, blinding and treatment allocation

Participants will be randomly assigned to either bCBT or CBT-TAU by an independent researcher, on the basis of a computer-generated block randomization table. Group allocation cannot be blinded to patients and therapists. However, outcome assessors (i.e., those conducting the SCID-I diagnostic interviews at T0 to T3) will be blinded to the allocation, in accordance to the CONSORT guidelines (Moher et al., 2010; Schulz et al., 2012).

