## Secondary study parameter(s)

Outcomes on continuous clinical outcome variables, such as depressive symptoms, at T1, T2 and T3 (week 6-10, 12-20, and 64-72) are estimated for descriptive purposes through mixed-model analyses (MM), with participants as random effects, and time (T1-T3), group (blended vs. face-to-face treatment) and time x group as fixed effects, with baseline scores as a single covariate. To assess the magnitude of treatment effects, Cohen’s *d* effect sizes (Cohen, 1988) for each time point are calculated by dividing MM parameter estimates of fixed effects at each post-treatment assessment by the pooled standard deviation of outcome measurements at baseline (T0).

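### The cost-utility ratio, and the cost increment in both ratios, are fixed as differences in arm means with no baseline covariate, which gives up precision that the collected EQ-5D and TiC-P baselines could supply

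*Protocol*

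**What the plan says.** Section 10.1 (Primary analyses, CEA/CUA) gives the estimator as a formula: "ICER =(mean costs blended eHealth treatment-mean costs TAU)/(mean bCBT -mean CBT-TAU"). In the prose that follows, the arm mean costs are subtracted, and "This difference will be then be divided with the subtracted effects (case of response or remission on the BAI"). The whole procedure is bootstrapped 10,000 times. The cost-utility ratio is said to be computed in the same way, with QALYs in place of response or remission. Neither ratio has a covariate.

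The same section also tests change in each cost domain and describes a repeated-measures multilevel model for costs, used for p-values and followed by a bootstrap of its parameters. It does not say whether the mean costs in the ratio come from that model.

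Section 10.2 does adjust for baseline, "with baseline scores as a single covariate", but only for continuous clinical outcomes and for descriptive purposes. Table 1 shows EQ-5D, BAI and TiC-P at T0 and at every later assessment. Visits are "at baseline (T0), week 6-10, week 12-20 and at weeks 64-72 (52 weeks follow-up"). Allocation is by a "computer-generated block randomization table", with patients "randomly allocated to either bCBT (n=78) or CBT-TAU (n=78").

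**The concern.** A QALY total built from utilities at T0 to T3 contains the baseline utility directly and is also correlated with it through the later utilities. Costs after randomisation can be expected to correlate with costs before it. A difference in arm means therefore carries whatever baseline difference chance has produced, and its standard error includes between-patient variation that the baseline value could explain.

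Two things are at stake. One is precision: wider uncertainty around the ratio and a flatter acceptability curve than the data allow. The other is conditional bias: in the one trial actually run, a visible baseline difference in utility or cost would pass partly into the result with no planned correction. The descriptive analyses are protected against this, while the analysis that drives the decision is not.

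**Working it through.** **1. The plan's own figure.** Section 4.4 gives z values 1.96 and 0.84, SD of costs 800, SD of effects 0.02, correlation 0.1 and "W=80,000, C=832,E=0,02". In its formula:

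- variance term = 800² + (80,000 × 0.02)² − 2 × 80,000 × 0.1 × 800 × 0.02 = 640,000 + 2,560,000 − 256,000 = 2,944,000
- net benefit difference = 80,000 × 0.02 − 832 = 768
- n per arm = 2 × 2.8² × 2,944,000 / 768² = 78.26

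The stated 78 per arm reproduces without any adjustment. Adjustment would add precision to this plan; it does not repair a faulty sample size.

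**2. Variance saved on the QALY difference.** Assumptions: assessments at weeks 0, 8, 16 and 68 (inside the protocol's windows), trapezoid QALYs, equal utility SD at each visit, equal correlation r between any two visits, no dropout. The protocol gives no r.

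Trapezoid weights in weeks are 4, 8, 30 and 26. They sum to 68, their squares sum to 1,656, and the three post-baseline weights sum to 64. Per unit of SD²:

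- variance of a QALY total = (1 − r) × 1,656 + r × 68²
- covariance with baseline = 4 + 64r
- share of variance removed = (4 + 64r)² / [(1 − r) × 1,656 + r × 4,624]

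| r | (4 + 64r)² | variance | share removed |
|---|---|---|---|
| 0.3 | 538.2 | 2,546.4 | 21% |
| 0.5 | 1,296.0 | 3,140.0 | 41% |
| 0.7 | 2,381.4 | 3,733.6 | 64% |

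The SD cancels, so the share does not depend on it. As an illustration at an assumed SD of 0.20 and r = 0.5, the SE of the QALY difference is 0.20 × √(2/78) × √3,140 / 52 = 0.035 unadjusted, and 0.035 × √(1 − 0.413) = 0.026 adjusted.

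**3. Weaker late correlation.** Keep every correlation at 0.5 except baseline with week 68, set to 0.2. The covariance is 4 + 0.5 × 38 + 0.2 × 26 = 28.2 and the variance is 3,140 − 2 × 0.3 × 4 × 26 = 3,077.6. The share removed is 28.2² / 3,077.6 = 26%, down from 41%.

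**4. Chance imbalance in baseline utility.** With 78 per arm, SE = SD × √(2/78). The baseline SD is assumed; section 4.4 gives only an SD of effects.

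| assumed SD | SE | P(absolute imbalance > 0.02) |
|---|---|---|
| 0.02 | 0.0032 | about 4 in 10¹⁰ |
| 0.05 | 0.0080 | 1% |
| 0.10 | 0.016 | 21% |
| 0.20 | 0.032 | 53% |
| 0.25 | 0.040 | 62% |

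The 95% bound reaches 0.02 at SD = 0.02 / (1.96 × √(2/78)) = 0.064.

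**5. What reaches the QALY.** A utility imbalance shifts the QALY difference by (w0 + r × w_rest) times itself. Here w0 is half the first interval (0.058 to 0.096 years over the protocol's windows) and w_rest is 1.17 to 1.29 years. At r = 0.5, the probability that the shift exceeds 0.02 QALY is 5 to 9% for SD 0.10, 33 to 40% for SD 0.20 and 44 to 50% for SD 0.25. At r = 0 it is essentially zero for every SD tried.

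**6. Costs.** Adjusting for baseline TiC-P cost removes the square of its correlation with the cost total. The protocol gives no value for this, so no figure is put on it.

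**The case against.** The case against has real force, and most of it limits the size of the point.

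- **No validity error.** Under randomisation the difference in arm means is unbiased, and the bootstrap already reflects chance imbalance in its spread. A reader might infer that the ratio is biased or its uncertainty misstated; the documents do not support that.
- **Baseline BAI is not ignored.** A reader might take the bare arm-mean formula to mean that it is. Section 8.1 defines response as a reduction of at least 30% from the patient's own baseline BAI, and remission as that plus a total score below 11. That is not covariate adjustment, but baseline is built into the effect.
- **Baseline TiC-P is not wholly unused.** Change tests and a repeated-measures model are planned. What remains is that the link from that model to the ratio is not stated.
- **The 0.02 comparison.** It is tempting to say that chance imbalance can exceed the whole planned QALY gain. The protocol's only effect SD is 0.02, and with a baseline SD of that size such an imbalance is practically impossible. That figure is labelled as the SD of effects, not of baseline utility, so it does not settle the question either way. The statement needs an assumed baseline SD of about 0.1 or more, and material carry-over before it holds in QALYs.
- **Detail for the SAP.** Covariates are often left to the SAP, which is not shown. Here, however, section 10.1 writes out the estimator, so the point is a stated choice and not silence. The absence of stratification in section 8.2 is silence, and is not pressed.

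**Conclusion.** The point holds as a matter of efficiency, for the QALY increment and for the cost increment of both ratios. The protocol targets an "80% chance (i.e., power) to be 95% confident that the therapy is good value", yet its primary estimator uses no baseline covariate although the data are in hand. The variance forgone on the QALY difference is about 21% to 64% for an equal correlation of 0.3 to 0.7, and less if baseline utility predicts the final visit weakly (26% in the example, against 41%). Those correlations are assumptions. Exposure to an imbalance comparable to 0.02 is conditional on a baseline utility SD of about 0.1 or more, also an assumption. The unadjusted analysis remains valid. Label: free improvement.

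**What to change.** In section 10.1, or in the SAP with a reference from it:

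- Estimate the incremental QALY adjusted for baseline EQ-5D utility, and the incremental cost adjusted for baseline TiC-P cost. Fit the two jointly so that their correlation is kept, for example by a bootstrapped seemingly unrelated regression. Centre and type of anxiety disorder may be added as covariates.
- Where QALYs are derived from the SF-36, use the baseline utility from that instrument in the same way.
- State how the multilevel cost model feeds the ratio, or that it serves only the p-values.
- Use the adjusted increments in both ratios and in the acceptability curve.
- For response and remission, baseline BAI may be added as a covariate, with the result expressed as a difference in proportions.
- Keep the unadjusted arm means as a sensitivity analysis.
- If imbalance is compared with the planned 0.02 QALY, state the baseline utility SD that is assumed.

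The cost is a paragraph of text and the analysis code. No further data, visits or patients are needed. The covariates should be fixed before outcome data are compared by arm.
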